### Park observations and imagery

The positive visual exposures of interest include the presence of people using the park, signage, mowing and other signs of care [114], diversity of plants and birds and greenness. Negative visual exposures include the presence of litter, arson, graffiti and broken windows of buildings along the park perimeter (called signs of disorder). We will employ two methods to obtain these data. First, Audubon volunteers will inventory plants in quadrants and count bird species using point counts less than three hours after sunrise, measuring species abundances [115, 116]. Volunteers will be trained by Audubon, and inter-observer reliability assessed by having two or more observers collect data simultaneously but independently [117]. Plant/bird species richness and biodiversity measurement will employ the well-established Shannon Diversity and Simpson Indexes [118, 119] and Evar Evenness Index [116]. Trained graduate students will also make observations of signs of care and the System for Observing Play and Recreation in Communities (SOPARC) [120]. SOPARC provides an assessment of park users’ PA levels, gender, activity types, and estimated age and ethnicity groupings as well as information on a park’s level of accessibility, usability, supervision, and organization with a high internal correlation between items (r = 0.75) [120], and exhibiting high inter-rater reliability (0.80–0.99) [117]. All nine parks, each of which consists of only one target area due their small size, will be observed twice over one day (9 am-2 pm) during randomly scheduled days without rain in summer months, by two raters. INT and CNT parks will be observed at the same time on different days for parallel observations. Signs of care involve observations (presence/absence) of manmade and natural items in a park and provides a categorical quality rating for each item, which is based on qualitative work in Detroit [114]. Second, we will measure visual greenness and negative visual exposures (signs of disorder) via 360^°^ images captured along each park perimeter, using a mounted camera (Samsung Gear 360). Images will be used to measure visual greenness, by quantifying pixels of greenery using methods we developed [121]. Images will also be used to assess negative exposures using Marco et al.’s neighbor disorder coding protocol [122], which has shown acceptable ICCs (0.41–0.60) for the mean level of subscales of physical disorder and decay and has also been validated (showing high correlations) with physical audits, police impressions, and neighborhood socioeconomic status. This virtual auditing approach has been validated across several samples [123, 124].

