
We will employ two weighting schemes to create individual-level visual exposures from the park measures. First, we will weight each exposure by the actual contact time spent within view of the park in the one-week observation time using the GPS data [59], as described previously. Second, we will calculate the percentage of the viewshed occupied by the park, as seen from the participant’s home by capturing a 360° image from the front door of the home location. We will then create weights using these measures, to be applied to each of the visual exposures above.

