To address missingness in our response data, we will employ strategies for imputation [139]. The techniques described above allow missing at random (MAR). Inverse probability weighting [140] will be investigated to accommodate missing data patterns that are not MAR. To minimize bias in analysis, we will adjust for factors that may be unbalanced between groups and examine the robustness of our conclusions under deviations of model assumptions. Below, we outline specific analyses for each hypothesis to be tested.

#### Hypothesis 1

We will separately evaluate average activity counts/minute and average moderate-to-vigorous minutes over the one-week observation period for each of the data collection periods. The predictor of interest is binary: INT versus CNT.

#### Hypothesis 2

The primary outcome, ‘green PA’, will be average activity counts/minute and average moderate-to-vigorous minutes over the one-week observation period while in parks and greenspaces in Detroit, as a subset of all activity.

#### Hypothesis 3

We hypothesize there will be an association between PA and the visual and auditory exposures. Instead of a binary predictor of interest, we will use continuous predictors for visual and auditory park exposures. Interaction terms between positive and negative exposures will also be assessed, as evidence suggests that negative sounds deplete the restorative benefits of natural sounds, [141] and that parks are often dominated by noise [45, 142].

#### Hypothesis 4

Each stress outcome will be evaluated separately and treated continuously. We will also explore potential mediators (e.g., PA) by adding each to mixed models as fixed terms, and adjusted mediation and partial correlation coefficients explored. We will adjust for prescription medication history and symptoms of acute illness as potential confounders.

#### Hypothesis 5

We will assess relationships with each stress indicator, in turn.

#### Hypothesis 6

We hypothesize there will be an association between each stress indicator and these exposures.

#### Hypothesis 7

We will compare INT and CNT groups from baseline through three-years post-restoration for changes in CRP and A1C (continuously measured) between INT and CNT groups. We will also consider the inclusion of prescription medication history and symptoms of acute illness as potential confounders.

#### Hypothesis 8

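### A positive-by-negative product of two visual exposures that share one participant weight contains that weight squared, so levelling-off returns to park contact can look like depletion by negative sights

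*Protocol article*

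**What the plan says.** The section on park observations and imagery defines both kinds of visual exposure at park level. For the positive ones: "The positive visual exposures of interest include the presence of people using the park, signage, mowing and other signs of care", together with species diversity and greenness. For the negative ones: "Negative visual exposures include the presence of litter, arson, graffiti and broken windows of buildings along the park perimeter".

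The same section then makes them individual: "We will employ two weighting schemes to create individual-level visual exposures from the park measures". Under the first scheme, "we will weight each exposure by the actual contact time spent within view of the park", from GPS. Under the second, "we will calculate the percentage of the viewshed occupied by the park", as seen from the participant's home. Both schemes cover positive and negative measures alike: "We will then create weights using these measures, to be applied to each of the visual exposures above".

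For Hypothesis 3, the statistical analysis section replaces the binary group indicator: "we will use continuous predictors for visual and auditory park exposures". It adds: "Interaction terms between positive and negative exposures will also be assessed, as evidence suggests that negative sounds deplete the restorative benefits of natural sounds". The reason given concerns sound, but the terms are announced for positive and negative exposures in general, directly after a sentence that names both visual and auditory exposures.

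The general model lists GROUP, TIME and their interaction as the minimum, plus a measure of exposure. It names no separate or non-linear term for contact time or viewshed share. Auditory exposures come from kriging (Neighborhood soundscapes), with no contact-time weight stated.

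**The concern.** Write P and N for the positive and negative score of a park in a given year, and w for the participant's weight. The weighted exposures are wP and wN, and their product is w²PN. P and N are the same for everyone at one park in one year, so within a park-year all variation in the product comes from w². The interaction coefficient therefore picks up any bend in the relation between outcome and contact.

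The direction matters. Depletion of a benefit for physical activity would appear as a negative interaction. A relation that rises and then flattens also gives a negative coefficient, with no role for litter or disorder. The study could then report that disorder cancels the benefit of restored greenery when it has only seen diminishing returns to time near the park. The Discussion presents individual-level positive and negative exposures as an important feature of the study, so this inference deserves protection.

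**Working it through.** **The plan's own figures.** The article gives no figure for this test. Its 82% power is for the difference-in-differences contrast. A normal approximation comes close: with 200 vs 250 participants, r = 0.35, ρ = 0.004 and 50 per park, the variance is 2[(0.65)(0.996) + 50(0.004)](1/200 + 1/250) = 0.01525, so SE = 0.1235. Then 0.35/0.1235 − 1.96 = 0.87, or about 81% power. Nothing below depends on it.

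**Algebra.** (wP)(wN) = w²PN. P and N take at most 9 parks × 4 times = 36 values.

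**A case to check by hand.** Let P = N = 0.5 everywhere, so the product is 0.25w². Let the outcome depend on contact only, as ln(1 + w), at w = 1, 3 and 8: 0.693, 1.386 and 2.197. The slopes are 0.693/2 = 0.347 and 0.811/5 = 0.162. The coefficient on w² through these points is (0.162 − 0.347)/(8 − 1) = −0.026, so the coefficient on the product is −0.026/0.25 = −0.105. N has no effect, yet the interaction is negative. With an outcome linear in w both slopes are equal and the coefficient is 0.

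**Simulation, single wave.** From the article: 9 parks, 50 people each, two-sided 5%. Assumed: P and N independent and uniform on 0.2 to 0.8, no effect of either, park fixed effects, and contact time lognormal with median 3 h/week and log-SD 1. The fitted terms are wP, wN and their product.

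| Response to contact | 2% of variance | 5% | 10% |
|---|---|---|---|
| log(1+w) | 24% | 52% | 84% |
| square root | 16% | 28% | 55% |

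These are false rejections, nearly all negative. Separate runs agreed within a few points. With a linear response, rejection was 4 to 7%. With a narrower weight (log-SD 0.5) and 2% of variance it was 12 to 14%. Although P and N were independent, wP and wN correlated at 0.85 to 0.89.

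**Simulation, four waves.** This used GROUP, TIME, GROUP×TIME, a random intercept and participant-robust errors. Significantly negative results (nominal 2.5%) were as follows.

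- Contact-time weight, concave response: 49 to 68% in the base setting, and 14 to 61% over other assumed spreads of w and P.
- Contact-time weight, linear response: the mean interaction was about 0 if the outcome was linear in wP. If it was linear in w alone, 16.6% were still significantly negative, because wP and wN stand in for w only imperfectly.
- Home-view weight, concave response: the mean was again negative, but only 3 to 6% were significant. The single-wave set-up, with 70% of weights zero, gave 8 to 54%, so this result depends heavily on the model and the assumed spread.
- Weighted visual by unweighted sound: mean about 0.001, with 4 to 5% significantly negative, so no negative bias.

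**Candidate remedies.**

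- Four waves, adding only w and w²: enough if the outcome depends on contact alone (about 5% significantly negative), but not if the effect of contact also scales with park quality (33 to 44%).
- Four waves, entering P, N, P×N, a flexible w, wP and wN separately: 2 to 3% in every setting.
- Single wave, testing w×P×N beside w, a curved term in w, and w times each centred score: about 4 to 7% two-sided.
- The same single-wave test when park slopes on w differ for unrelated reasons (SD 0.15 to 0.20 of the outcome SD, assumed): 15 to 23%, because the term rests on differences between nine parks.
- Power of that test when true depletion explained 10% of variance, single wave: about 7%, against about 10% for the product of weighted exposures.

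**The case against.** The strongest reply is that the article does not fix the model that is being faulted. Its predictors are given as a minimum, time in view of the park appears in Table 1 as a measure in its own right, no Hypothesis 3 equation is written, and a general check of robustness to model assumptions is promised. How an interaction is coded is often left to the analysis plan. The rationale, moreover, concerns sounds, and sound-by-sound terms carry no shared weight.

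Part of this stands. The article does not write out a visual-by-visual product, and a fuller plan could already model w. But the two choices it does state, one common multiplicative weight and positive-by-negative interactions for exposures in general, lead to w²PN when carried out as written. A general promise of robustness checks does not commit anyone to modelling w.

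A reader might infer more than the documents support.

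- That the interaction test is invalid whatever the data. It is not: serious inflation needs a concave response, which the article neither states nor excludes.
- That both weighting schemes are equally exposed. The evidence for the home-view weight is weaker and mixed.
- That the stress analyses suffer in the same way. No interaction is announced for Hypothesis 6, so this is conjecture.
- That the trial's main conclusions are at risk. Hypotheses 1, 2, 4, 7 and 8 compare intervention with control neighbourhoods and do not use this term.

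**Conclusion.** The point holds for visual-by-visual interactions formed from the weighted exposures. The presence of w² follows from the article's own construction. The false depletion signal is conditional: with a concave response to contact time, log-SD 1 and 2 to 10% of variance explained, about 15 to 85% of single-wave runs were falsely significant, nearly all in the negative direction. With a linear response in that set-up the rate is about nominal. The spread of the weights, the response shapes and the variance explained are assumptions; none is in the documents. This affects a secondary association analysis. It should be corrected before the analysis, but it does not threaten the primary comparison.

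**What to change.** In the statistical analysis section, under Hypothesis 3, state for visual-by-visual interactions that:

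1. the weight w enters as its own term with a flexible curve (for example a log, square-root or spline term);
2. the unweighted, centred park scores P, N and P×N enter, together with w×P and w×N (P and N can change from year to year, so park effects alone do not absorb them);
3. depletion is tested by w×P×N, and not by a product of two weighted exposures;
4. the slope on w may vary by park, through a random slope or inference at park level, because P and N take one value per park per wave;
5. visual depletion is reported as exploratory.

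Sound-by-sound and visual-by-sound terms can stay as planned. The change is to wording and model code and needs no new data. The cost is several extra terms and an interaction test with low power: with nine parks a null result would say little. The version with park-varying slopes was not itself simulated, so its error rate with nine parks should be checked before it is adopted.

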## Methods

### Design

The overall design of StAND is a four-year quasi-experimental, natural experiment, with two conditions (INT and CNT), four measurement occasions, and individual-level measurement of exposures and outcomes (see Fig. 1 for a conceptual diagram for the study). Four INT parks were selected by Detroit Audubon and five comparable CNT parks were selected, based on size, existing trees/plants, and proximity to other bird habitats. All adults (i.e. aged ≥18 years) living in a CNT or INT park neighborhood (defined in the following text) were invited to participate. Baseline (t = 0) and three annual measurements (t = 1 to t = 3) post-restoration will be conducted on participating individuals with the intention of having a longitudinal panel study design. However, we considered sampling alternatives depending on attrition, as others studies have done [42]. If attrition is higher than expected (> 25% at t = 1), then additional participants will be recruited at each time point, yielding a repeated cross-sectional design, with a nested panel. If assessments at certain time points are missing within the panel for some participants, we will assume that data from our unbalanced panel is missing at random.

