### Sample size

Assuming a longitudinal panel design, sample size assessments for the study are based on achieving 82% power to test the hypotheses. The effect measure is a difference-in-differences (DID) — in hypotheses 1–3, i.e., the expected change in PA from baseline to three-years post-restoration in INT parks compared to the corresponding change in CNT parks. Hypotheses 3–6 concern a DID in stress outcomes. A review of the literature on PA [46] and cortisol [47] suggests an effect size (EF) of 0.35 could be posited. Accordingly, we calculate our sample size requirements to detect an EF of 0.35 or better with 82% power. Two other design features are: a serial correlation *r* between repeated measures over time and intra-class correlation (ICC) *ρ* for clustering within neighborhood parks. In community-intervention studies such as ours, *ρ* is small [48–51]. Plausible values from the literature and our own experiences, suggest *r* ≥ 0.35 and *ρ ≤* 0.004. With a total of nine parks (4 INT, 5 CNT), we will need a sample of 450 participants, or 50 per park, to detect EF = 0.35 with 82% power, based on a two-sided test at significance level 5%. Because attrition is expected over the study period, we will recruit a total of 620 participants at t = 0 (baseline) to account for attrition of 15% at t = 1 and another 10% at t = 2 and 5% at t = 3. Our sample size assessment may also be deemed conservative as it does not account for potential influence of fixed covariates, which should increase precision on the intervention effect estimate by reducing residual variance resulting in a positive effect on power.

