We will compare INT and CNT groups from baseline through three-years post-restoration for changes in blood pressure, hip-to-waist ratio and BMI (continuously measured) between INT and CNT groups.

Despite our best effort to recruit and retain a longitudinal panel of participants, we may face problems with attrition higher than the projected attrition rates of 15% at t = 1, another 10% at t = 2, and 5% at t = 3. With these levels, our longitudinal panel becomes unbalanced but valid inference can be made under the assumption that attrition is at random (MAR). We describe another strategy, *repeated cross-sections*.

By repeated cross-sections we mean a series of independent samples are drawn at the subsequent times t = 1, 2, 3 following the initial baseline sample at t = 0. It could happen that a participant in the baseline sample is also in any of the subsequent samples, but this is at random. With repeated cross-sectional samples, we cannot estimate *within participant* change in outcomes, which is the key advantage of the longitudinal panel approach. However, we can still assess patterns of change at an aggregate level as explained in the following text.

Consider an outcome $$ {\mathit{\mathsf{Y}}}_{\mathit{\mathsf{it}}} $$ at time *t* in the *i-*th participant, and the linear model $$ {{\textsf{Y}}}_{{\textsf{i}\textsf{t}}}={\mathbf{\textsf{x}}}_{{\textsf{i}\textsf{t}}}^{\prime}\beta +{\alpha}_{{\textsf{i}}}+{\varepsilon}_{{\textsf{i}\textsf{t}}} $$ with exogenous covariates $$ {\mathbf{\textsf{x}}}_{{\textsf{it}}} $$, *t* = 0, 1, 2, 3. We aggregate each sample into *C* cohorts defined as participants who share common characteristics such as age, sex, neighborhood park, etc. Aggregation of participants to the cohort level *c* replaces the model by the cohort model $$ {\overline{{\textsf{Y}}}}_{{\textsf{c}\textsf{t}}}={\overline{{\mathbf{\textsf{x}}}^{\prime}}}_{{\textsf{c}\textsf{t}}}\beta +{\overline{\alpha}}_{{\textsf{c}}}+{\overline{\varepsilon}}_{{\textsf{c}\textsf{t}}} $$, *c* = 1, …,*C*, *t* = 0, 1, 2, 3. (Bar notation refers to averages over participants within cohort/time). Our observed data become a pseudo-panel of repeated observations on cohorts over time, and estimation of differences between INT and CNT cohorts could be compared over time, although the cohorts are not comprised of the same participants from one time point to the other. Some technical issues will need to be addressed to ensure a consistent estimator of *β* [143–146].

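### The fallback for excess attrition is a topped-up panel in one section and independent samples in another; followed literally, the second has about 66% power, not 82%

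*Protocol article*

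**What the plan says.** The protocol article describes the response to high attrition twice.

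- **Design.** If more than 25% are lost at t = 1, "additional participants will be recruited at each time point, yielding a repeated cross-sectional design, with a nested panel". People already enrolled stay, and new people join them. The same section treats an unbalanced panel as missing at random.
- **Statistical analysis, closing text.** The concern there is attrition above 15% at t = 1, a further 10% at t = 2 and 5% at t = 3. The article first says that an unbalanced panel still allows valid inference under missing at random. It then offers another strategy: "By repeated cross-sections we mean a series of independent samples are drawn at the subsequent times". A baseline participant may reappear, but only at random. Within-participant change is said to be inestimable. People are averaged into cohorts by age, sex, park and similar traits, and cohort means are modelled over time, "although the cohorts are not comprised of the same participants from one time point to the other".
- **Sample size.** "Assuming a longitudinal panel design, sample size assessments for the study are based on achieving 82% power to test the hypotheses". Power refers to a difference-in-differences, "the expected change in PA from baseline to three-years post-restoration in INT parks compared to the corresponding change in CNT parks". No power is given for either form of the fallback.

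**The concern.** A top-up that keeps a nested panel has overlap by design. A series of independent samples has overlap by accident. One fallback cannot be both, and the two descriptions also start at different attrition levels. With 20% lost at t = 1, for example, the Statistical analysis text is already in play and the Design text is not.

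The choice affects the primary contrast. The sample size relies on people being measured at both baseline and year 3, so a design that draws fresh people loses part of the precision the study was sized on. If the panel is topped up but the data are handled as cohort means, the analysis starts from a premise the data do not meet and does not use individual histories. Either way the decision would be taken after attrition has been seen, with no rule for choosing.

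**Working it through.** **Inputs (Sample size section).** Effect size: the literature "suggests an effect size (EF) of 0.35 could be posited", taken here as SD units of the outcome. Correlations: the article's values "suggest *r* ≥ 0.35 and *ρ ≤* 0.004", used at r = 0.35 and ρ = 0.004. Four INT and five CNT parks with 50 people each give 200 against 250. The test is two-sided at 5%. Power = Φ(0.35/SE − 1.96). Design effect D = 1 + 49 × 0.004 = 1.196. Also 1/200 + 1/250 = 0.009.

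**Step 1: reproduce the plan's 82%.**
- ICC as a multiplier: SE² = 2(1 − 0.35) × 1.196 × 0.009, SE = 0.118, power 84.1%.
- ICC as a park-by-time component: SE² = 2(0.65 + 0.196) × 0.009, SE = 0.123, power 81.0%.

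The stated 82% lies between the two. Recruitment also agrees: 620 × 0.85 × 0.90 × 0.95 = 450.6.

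**Step 2: independent samples, as the Statistical analysis text defines them (r = 0).**
- 450 at each occasion: SE² = 2 × 1.196 × 0.009, SE = 0.147, power 66.5%. Both ways of entering the ICC give this.
- 620 at baseline, 450 at year 3: with arms in the ratio 4:5, the arm factor is 9/4 + 9/5 = 4.05. SE² = (1/620 + 1/450) × 4.05 × 1.196, SE = 0.136, power 72.8% (71.6% with the park-by-time form).
- Returning to 82% with r = 0 would need about 80 per park, or 720 per occasion.

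**Step 3: top-up, as the Design section defines it.** Assumptions not in the article: 25% to 40% lost at t = 1, later losses as planned, and a top-up to 450 at year 3.
- Retained from baseline: 620 × 0.75 × 0.90 × 0.95 = 398, or 620 × 0.60 × 0.90 × 0.95 = 318. That is 88% or 71% of 450, so overlap is not by chance.
- Contrast of wave means with overlap n_p: SE² = (1/620 + 1/450 − 2 × 0.35 × n_p/(620 × 450)) × 4.05. Without D, SE = 0.107 (398) or 0.111 (318). With D, power is 85% or 82%.
- Person-level generalised least squares on pairs and singles, with D: power 86% or 84% (82.4% or 80.7% with the park-by-time form).

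**Step 4: does the cohort model lose the correlation in the top-up case?** The article's cohort model carries a cohort effect with no time subscript. When most members are the same people, their cohort means are correlated over time and that effect absorbs the shared part. Simulating it (effect taken as fixed, D omitted) gave model-based and empirical SEs of about 0.106–0.112. That matches the overlap values of 0.107–0.111 in step 3. It does not match 0.125, the value if all people were treated as different: (1/620 + 1/450) × 4.05 = 0.01553, square root 0.125. The cost of aggregation is therefore the step 3 gap, 86% against 85% or 84% against 82%.

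**Step 5: dropout.** A likelihood-based mixed model conditions on each person's observed outcomes, so dropout that depends on earlier observed outcomes is accommodated under missing at random. Cohort means compare whoever is present at each wave, and a cohort effect does not correct for who left within the cohort. In an illustrative simulation with dropout depending on baseline and differing by group, the person-level model stayed unbiased and the cohort contrast was biased. The size of the bias depends on the dropout assumed, so no figure is given.

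**The case against.** Several points on the other side have force.

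- **Precision under the top-up.** A reader might infer that the cohort model throws away the repeated measures and inflates the standard error by 12–19%. The documents do not support that. The inflation appears only if the analysis is taken to be a contrast of two unrelated samples, whereas the article's model includes a cohort effect that persists over time (step 4).
- **Mixing scenarios.** The 66% and 73% figures hold only if independent samples are actually drawn. In that case no within-person data exist to be discarded, and the article openly concedes that within-participant change is lost. They must not be read as the power of the topped-up panel.
- **The mixed model is not withdrawn.** The article says an unbalanced panel is valid under missing at random, presents repeated cross-sections as another strategy, and notes technical issues still to be settled. A reader might infer that linked data on retained people will be ignored; no sentence says so. Some of this detail may belong in a fuller document.

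These points limit the size of the problem but do not remove the contradiction. The two sections use the same name for different sampling schemes with different triggers. If they are meant as separate contingencies, the article gives no rule for choosing between them and names no analysis specifically for the nested-panel version. The only analysis described under repeated cross-sections is the pseudo-panel.

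**Conclusion.** The contradiction stands on trigger, sampling and analysis. Its size depends on which description is followed.

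- **Independent samples:** power falls from the stated 82% to about 66% at 450 per occasion, or 73% with 620 at baseline.
- **Topped-up panel:** the loss of power from using cohort means is small, about 1–2 points under the step 3 assumptions. The more serious costs are a premise that is false for the data and weaker protection when dropout depends on earlier outcomes.

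All power figures use the plan's inputs, a normal reference and an effect size in outcome SD units. With 7 degrees of freedom for nine parks they drop to about 72% (panel) and 54% (independent samples); the gap remains, and the degrees of freedom are a separate matter. Under independent sampling, cohorts built on strong predictors might recover some variance, by an amount the documents do not allow to be calculated. The point should be corrected before attrition is known. It is conditional on the fallback being used.

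**What to change.** 1. Give one trigger and one sampling scheme for the fallback in both sections: the Design section's retained panel plus top-up recruits. Replace the independent-samples definition in the Statistical analysis section.
2. Name the generalised linear mixed model already planned as the fallback analysis, fitted to all person-waves, with participant nested in park and top-up recruits contributing the waves they have.
3. Keep the cohort pseudo-panel as a sensitivity analysis only.
4. State in the Sample size section that the 82% applies to the longitudinal panel. If independent sampling is kept as an option, give its own power.

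The cost is wording in the protocol and analysis plan. The model is already planned, and no new kind of data is required.
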